## Abstract

**Background:**

Fractures of the distal radius are common and account for an estimated 17% of all fractures diagnosed. Two-thirds of these fractures are displaced and require reduction. Although distal radius fractures, especially extra-articular fractures, are considered to be relatively harmless, inadequate treatment may result in impaired function of the wrist. Initial treatment according to Dutch guidelines consists of closed reduction and plaster immobilisation. If fracture redisplacement occurs, surgical treatment is recommended. Recently, the use of volar locking plates has become more popular. The aim of this study is to compare the functional outcome following surgical reduction and fixation with a volar locking plate with the functional outcome following closed reduction and plaster immobilisation in patients with displaced extra-articular distal radius fractures.

**Design:**

This single blinded randomised controlled trial will randomise between open reduction and internal fixation with a volar locking plate (intervention group) and closed reduction followed by plaster immobilisation (control group). The study population will consist of all consecutive adult patients who are diagnosed with a displaced extra-articular distal radius fracture, which has been adequately reduced at the Emergency Department. The primary outcome (functional outcome) will be assessed by means of the Disability Arm Shoulder Hand Score (DASH). Secondary outcomes comprise the Patient-Rated Wrist Evaluation score (PRWE), quality of life, pain, range of motion, radiological parameters, complications and cross-overs. Since the treatment allocated involves a surgical procedure, randomisation status will not be blinded. However, the researcher assessing the outcome at one year will be unaware of the treatment allocation. In total, 90 patients will be included and this trial will require an estimated time of two years to complete and will be conducted in the Academic Medical Centre Amsterdam and its partners of the regional trauma care network.

**Dicussion:**

Ideally, patients would be randomised before any kind of treatment has been commenced. However, we deem it not patient-friendly to approach possible participants before adequate reduction has been obtained.

**Trial registration:**

This study is registered at the Netherlands Trial Register (NTR3113) and was granted permission by the Medical Ethical Review Committee of the Academic Medical Centre on 01-10-2012.

## Background

Fractures of the distal radius account for an estimated 17% of all fractures diagnosed [1,2]. Two-thirds of these fractures are displaced and require reduction [3]. Although extra-articular distal radius fractures are considered to be relatively harmless, inadequate treatment may result in severely impaired function of the wrist [4,5]. The consequences of post-traumatic loss of function are comprehensive, both on individual and societal level, and have long been underestimated [6].

Several treatment modalities to obtain and maintain reduction exist and decision-making is mainly based on fracture type, region and surgeon’s preference [7]. Although good results have been described for both conservative and surgical management, the ideal treatment method remains unknown.

According to current Dutch guidelines, standard treatment for patients with displaced extra-articular distal radius fractures consists of closed reduction and cast immobilisation for four to six weeks [8]. Nevertheless, redisplacement occurs in up to 60% of cases and functional recovery is frequently poor [9-11]. If fracture redisplacement occurs, surgical reduction and fixation is the treatment of choice [8].

A well-established and widely applied surgical approach is open reduction and internal fixation (ORIF). This procedure involves surgical (open) fracture reduction and internal fixation by means of locking plates. Over the past years, the use of volar locking plates has become increasingly popular [12]. This type of osteosynthesis requires a relatively simple volar approach to the wrist, followed by fracture fixation using fixed angle implants [13]. The technique allows more accurate reduction and immediate stable fixation. Subsequent removal of the plate is rarely necessary [7,14]. The fracture stability allows for early mobilisation and may therefore result in an improved recovery of function [7,14]. By 1987 already, Dias et al. concluded that patients who were encouraged to mobilise their injured wrist from the start in a modified cast which only restricted extension, recovered function more quickly than those whose who were immobilised in a conventional plaster cast [10].

A recent randomised controlled trial by Arora et al. compared open reduction and internal fixation with a volar locking plate with closed reduction and plaster immobilisation. They included patients of 65 years and older who had suffered all types of displaced distal radius fractures with inadequate reduction or redisplacement [15]. The operative treatment group showed better wrist function in the early post-operative period. However, at six and twelve months there were no significant differences in wrist function between treatment groups. At all times, grip strength was significantly better in the operative group. These results are consistent with a previous retrospective cohort study among elderly patients conducted by Arora et al. as well [16]. Future studies compare the quality of life between patients treated with a volar locking plate or closed reduction and plaster immobilisation [17].

Despite the high incidence of displaced distal radius fractures and the substantial possible implications of suboptimal management, no high level evidence regarding the best treatment method yet exists. To our knowledge, no studies have been performed comparing conservative treatment with ORIF in patients of all ages with displaced extra-articular distal radius fractures. Therefore, we are proposing to conduct a randomised controlled trial to compare the functional outcome, assessed with the Disability Arm Shoulder Hand Score (DASH), after ORIF with a volar locking plate with closed reduction followed by plaster immobilisation, in patients with displaced extra-articular distal radius fractures. We hypothesise that surgical reduction will result in a more rapid recovery and better functional results at one year follow up than conservative treatment consisting of closed reduction and plaster immobilisation.

The aim of this study is to compare two treatment methods for patients with displaced extra-articular distal radius fractures regarding functional outcome at one year follow up. These treatment methods include open reduction and internal fixation (ORIF) with a volar locking plate and closed reduction followed by plaster immobilisation.

## Methods/Design

This single blinded randomised controlled trial will randomise between open reduction and internal fixation (ORIF) with a volar locking plate (intervention group) and closed reduction followed by plaster immobilisation (control group).

### Participants

The eligible study population will consist of all consecutive adult patients who are diagnosed with a displaced extra-articular distal radius fracture, which has been adequately reduced at the Emergency Department of the Academic Medical Centre Amsterdam or one of the other participating hospitals.

### Inclusion criteria

• Patients ≥ 18 years and ≤ 75 years

• Extra-articular (AO type A) displaced distal radius fracture, as classified on lateral, posterior-anterior and lateral carporadial radiographs by a radiologist or trauma surgeon.

• Acceptable closed reduction obtained according to current Dutch guidelines [1].

•<15° dorsal or <20° volar angulation of the distal fracture fragment

•<5 mm loss of radial height

•≥15° radial inclination

### Exclusion criteria

• Open distal radius fractures

• Multiple trauma patients (Injury Severity Score (ISS) ≥16)

• Other fractures of the affected extremity

• Patients who indicate to have had impaired wrist function prior to injury, for example due to rheumatoid arthritis, neurological disorders of the upper limb or previous malunions in the affected limb.

• Patients suffering from disorders of bone metabolism known to adversely effect fracture healing, such as osteomalacia.

• Patients suffering from connective tissue or (joint) hyperflexibility disorders known to adversely effect fracture healing and/or soft tissue and wound healing.

• Patients unable to understand the treatment information and informed consent forms as judged by the attending physician.

### Interventions

All patients will initially be treated with closed reduction and cast immobilisation. This will take place under local anaesthesia by means of a haematoma block with 20 cc Lidocaine 1%. Closed reduction will be performed according to the Robert-Jones method [18]. This involves increasing the deformity first, then applying continuous traction and immobilising wrist and hand in the reduced position. Additional radiographs will be performed to verify the quality of the reduction (see Inclusion criteria). After this has been confirmed, the wrist will be immobilised according to Dutch guidelines: a dorsal splint for one week. Once informed consent is obtained, patients will be randomized at one week between open reduction and internal fixation with a volar locking plate, or continuation of cast immobilization.

The intervention group will be treated with open reduction and internal fixation with a volar locking plate. The surgery will be performed by a general, trauma or orthopaedic surgeon. In order not to disturb clinical practise, and to provide an accurate comparison of two treatment modalities as they are applied in clinical practise, no specific interval to surgery is prescribed. According to the current standard treatment protocol, antibiotic prophylaxis will be administered pre-operatively. The distal radius will be approached according to Henry, which involves an incision between the tendon of the flexor carpi radialis and the radial artery. The advantage of this approach is the possibility of an easy extension to the proximal or distal part of the forearm and the fact that the plate will be optimally covered by soft tissue [19]. Moreover, the median nerve is not at risk using this technique. After the fracture site is exposed, the fracture will be reduced and provisionally fixed with K-Wires and/or reduction forceps. An appropriate volar locking plate which best suits the anatomy of the wrist and the fracture type will be selected. Screw placement and fracture reduction will be confirmed intra operatively by radiographic images. Wound closure will be performed at the discretion of the surgeon using standard techniques and no post-operative fixation or immobilisation will be applied. During the first follow up visit at five to ten days, wound inspection will be performed. Patients will be instructed to use the affected extremity in daily activities as pain allows.

The control group will continue treatment with cast immobilisation according to Dutch guidelines: a circular cast for another four weeks [8]. At one week and three weeks following initial immobilisation, radiographs will be performed in both groups to ensure that loss of reduction has not occurred. Loss of reduction is defined as: >15° dorsal or >20° volar angulation of the distal fracture fragment, >5 mm loss of radial height, or ≤15° radial inclination [8]. If this is the case, operative treatment will be offered. According to Dutch treatment standards, vitamin C 500 milligrams will be prescribed to all patients at initial presentation and for a duration of two months in order to prevent Complex Regional Pain Syndrome [8].

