### Secondary outcomes

• Rist pain and disability expressed as change on Patients-Rated Wrist Evaluation Score (PRWE). The PRWE is a validated tool for assessing functional outcome in patients with distal radius fractures [21]. This score was first described in 1998 by McDermid et al. [22] and developed by expert surveys. The PRWE is a 15-item questionnaire designed to measure wrist pain and disability in activities of daily living. The PRWE allows patients to rate their levels of wrist pain and disability from 0 to 10, and consists of three subscales: Pain, Function and Cosmetics.

• Quality of Life assessed using the Short Form–36 (SF-36^®^) questionnaire. The SF-36 is a validated multipurpose, short form health survey which contains 36 questions representing eight different health domains [23]. These domains are combined into a mental and physical component scale. From each domain, scores ranging from 0 to 100 points are derived, with lower scores indicating poorer quality of life.

• Pain as indicated on a visual Analogue Scale (VAS), in which 0 implies no pain and 10 the worst possible pain. Patients will be asked to give an estimation of the type and quantity of pain medication taken during all follow up visits.

• Patient satisfaction at one year by simply asking patients if they are satisfied with the result (yes/no).

• Range of motion of the wrist measured on both sides with a handheld goniometer.

• Prehensile grip strength as measured with a Baseline dynamometer.

• Radiological parameters: radial inclination, volar/dorsal tilt, communition, ulnar variance and radial length measured digitally in the Picture Archiving and Communication System (PACS) on standard posterior anterior (PA), lateral carporadial and lateral X-rays of the wrist. Radiographs will be obtained according to standardised procedures. PA radiographs with the shoulder in 90 degrees abduction, elbow in 90 degrees flexion and the wrist in neutral position; lateral X-rays with the shoulder in neutral position and elbow in 90 degrees flexion; and the lateral carporadial radiographs will be obtained by positioning the lower arm on a 20-25 degrees angled wedge.

• Rate of cross-overs

• Complications such as: loss of reduction, fracture malunion or non-union, wound and/or plate infection, tendon irritation and/or rupture, neuropathy and the occurrence of complex regional pain syndrome according to the criteria by Veldman et al. [24].

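### A radial inclination of exactly 15° counts both as an acceptable reduction at entry (≥15°) and as loss of reduction at follow-up (≤15°)

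*Protocol article*

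**What the plan says.** In the protocol article, the Inclusion criteria list the limits for an acceptable closed reduction. For radial inclination the limit is "≥15° radial inclination", so 15° is acceptable.

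The Interventions section defines loss of reduction, to be checked on radiographs at one and three weeks in both groups. The last element of the definition, with its consequence, reads "or ≤15° radial inclination [8]. If this is the case, operative treatment will be offered". Here 15° counts as lost.

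The same section sets the time of allocation: "patients will be randomized at one week between open reduction and internal fixation with a volar locking plate". The first check for loss of reduction therefore falls at about the time of randomisation.

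Two secondary outcomes depend on the definition. One is the complications outcome, which begins "Complications such as: loss of reduction, fracture malunion or non-union". The other is "Rate of cross-overs". The Statistical analysis section compares conversions and complication rates with a Fisher exact or chi-square test.

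**The concern.** Acceptable reduction and loss of reduction should exclude each other. For radial inclination they share the value 15°. A wrist reduced to 15° qualifies for the trial, and the same wrist, unchanged on a later film, qualifies as having lost its reduction.

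The definition has a treatment consequence, so this is more than wording. A control patient with a stable fracture would be offered the intervention arm's treatment, would be counted as a complication, and would be counted as a cross-over on accepting. Sites could also settle the tie differently, which would make both counts inconsistent across hospitals.

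**Working it through.** **Boundary check.** The table applies the entry limits (Inclusion criteria) and the loss-of-reduction limits (Interventions) one unit below, at, and one unit above each cut-off.

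| Parameter | Entry limit | Loss limit | One unit below | At the cut-off | One unit above |
|---|---|---|---|---|---|
| Dorsal angulation | <15° | >15° | acceptable | neither | lost |
| Volar angulation | <20° | >20° | acceptable | neither | lost |
| Loss of radial height | <5 mm | >5 mm | acceptable | neither | lost |
| Radial inclination | ≥15° | ≤15° | lost | **both** | acceptable |

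The first three parameters use strict signs on both sides. A value on the cut-off is not eligible and does not trigger an offer of surgery. Radial inclination is the only parameter with an overlap, and the overlap is the single value 15°.

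**Does anything else settle the tie?** The Interventions section refers back to the Inclusion criteria for the quality of the reduction, and the Randomisation section asks only for adequate reduction. Neither says which limit governs at 15°. The two lists also cite different references for the Dutch limits, [1] at entry and [8] for loss of reduction.

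**How many patients?** The article gives neither a distribution of radial inclination after reduction nor a recording precision, so the size rests on assumptions.

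- Assumed: radial inclination X is normal, with mean m of 20° to 22° and SD s of 3° to 5°.
- From the Sample size section: 45 patients per arm.

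Share of eligible patients reading exactly 15°:

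- read to 1°: P(14.5 < X < 15.5) / P(X > 14.5)
- read to 0.1°: P(14.95 < X < 15.05) / P(X > 14.95)

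| m, s | Share, read to 1° | Of 45 controls | Share, read to 0.1° | Of 45 controls |
|---|---|---|---|---|
| 22°, 3° | 0.90% | 0.40 | 0.088% | 0.04 |
| 21°, 4° | 3.43% | 1.54 | 0.346% | 0.16 |
| 20°, 5° | 5.60% | 2.52 | 0.574% | 0.26 |

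The other two corners, read to 1°, lie inside this range: 1.56 of 45 at (20°, 3°) and 1.45 of 45 at (22°, 5°).

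**Two deductions.** Some patients who enter at 15° will truly redisplace, and they would be classed as lost under either sign. With the redisplacement of up to 60% given in the Background, the central figure could fall to 1.54 × 0.40 = 0.62 wrongly classed controls. For cross-overs, the patient must also accept surgery.

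**Scale.** Redisplacement of 60% would be 0.60 × 45 = 27 controls.

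**The case against.** The strongest reply is that this is one boundary sign with almost no consequence. Surgery is only offered, not required. DASH is analysed by intention to treat, so a borderline control who crosses over stays in the control arm. At most a patient or two is added to two secondary counts, against up to 27 genuine redisplacements. That is right, and it is why the point is minor.

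The size can also be challenged. The distribution is assumed, and the upper figures depend on whole-degree readings although the angles are measured digitally. Some patients at 15° would redisplace anyway. All of this is fair: the figure may well be below one patient.

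The timing is uncertain too. The article does not say whether the one-week film comes before or after allocation. If it comes before, the patient is not yet a control at that check, and the consequence for controls arises at three weeks. The contradiction remains, because the three-week check uses the same definition.

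Finally, the direction of the correction cannot be read from the article, since both limits are attributed to a guideline that is not at hand. That affects which sign to change, but not whether one must change.

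The conflict is between two printed rules, one of which triggers an offer of surgery. It is not a detail that a condensed article leaves to a fuller document.

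**Conclusion.** The concern holds. The entry limit and the loss-of-reduction limit for radial inclination both include 15°, and the article does not resolve the tie. The other three limits do not overlap and are not at issue.

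The point is minor. About 1 or 2 of 45 controls would enter at exactly 15° if angles are read to 1° (range 0.4 to 2.5), and under 0.3 if they are kept to 0.1°. Both ranges rest on the assumed normal distribution. They overstate the number wrongly classed, because some of these patients will truly redisplace, and they overstate cross-overs further, because not all will accept surgery. They do not cover fractures that enter above 15° and later read exactly 15°. The sign decides the class of those as well, but such a fracture may have moved.

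The loss-of-reduction and cross-over counts are affected slightly. The effect on the primary DASH analysis is negligible.

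**What to change.** Check the text of the Dutch guideline first, since the two lists cite different references for it. Unless it says otherwise, change the radial inclination limit in the loss-of-reduction definition (Interventions) from ≤15° to <15°. Every value then falls in exactly one class and eligibility is untouched. If the guideline places 15° itself on the unacceptable side, keep ≤15° there and change the entry limit (Inclusion criteria) to >15°.

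Use the same limit for eligibility, for the offer of surgery and for the loss-of-reduction outcome. The cost is one sign in the protocol and, if the trial is recruiting, a short notice to sites.

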### Randomisation

All patients diagnosed with an extra-articular AO type A1, A2 or A3 distal radius fractures will be requested to participate in this study. Patients will be eligible after adequate reduction of the fracture has been acquired. Upon obtaining informed consent, patients will be randomised into either the intervention group (ORIF with a volar locking plate) or the control group (closed reduction and plaster immobilisation). This will be performed online by randomisation software provided by the Clinical Research Unit of the Academic Medical Centre Amsterdam. In order to avoid any imbalances between treatment groups, patients will be randomised into three strata according to age: 18-30, 31-60 and >60 years using a block randomisation.

### Blinding

Randomisation status will not be blinded since the treatment allocated involves a surgical procedure.

### Primary outcome

The primary endpoint of this study is wrist function, pain and disability as measured with the DASH score at one year follow up [20]. The Disabilities of the Arm, Shoulder and Hand (DASH) score is a 30-item, self-report questionnaire designed to measure physical function and symptoms in patients with any or several musculoskeletal disorders of the upper limb. The DASH outcome measure is scored in two components: the Disability/Symptom and the optional high performance Sport/Music module. The DASH Disability/Symptom score is a summation of the responses to 11 questions on a scale of 1 to 5, with 0 (no disability) to 100 (severe disability). The questions test the degree of difficulty in performing a variety of physical activities because of arm, shoulder, or hand problems (6 items). It also investigates the severity of pain, tingling (2 items), as well as the effect of the upper limb problem on social activities, work, and sleep (3 items).

### Secondary outcomes

• Rist pain and disability expressed as change on Patients-Rated Wrist Evaluation Score (PRWE). The PRWE is a validated tool for assessing functional outcome in patients with distal radius fractures [21]. This score was first described in 1998 by McDermid et al. [22] and developed by expert surveys. The PRWE is a 15-item questionnaire designed to measure wrist pain and disability in activities of daily living. The PRWE allows patients to rate their levels of wrist pain and disability from 0 to 10, and consists of three subscales: Pain, Function and Cosmetics.

• Quality of Life assessed using the Short Form–36 (SF-36^®^) questionnaire. The SF-36 is a validated multipurpose, short form health survey which contains 36 questions representing eight different health domains [23]. These domains are combined into a mental and physical component scale. From each domain, scores ranging from 0 to 100 points are derived, with lower scores indicating poorer quality of life.

• Pain as indicated on a visual Analogue Scale (VAS), in which 0 implies no pain and 10 the worst possible pain. Patients will be asked to give an estimation of the type and quantity of pain medication taken during all follow up visits.

• Patient satisfaction at one year by simply asking patients if they are satisfied with the result (yes/no).

• Range of motion of the wrist measured on both sides with a handheld goniometer.

• Prehensile grip strength as measured with a Baseline dynamometer.

• Radiological parameters: radial inclination, volar/dorsal tilt, communition, ulnar variance and radial length measured digitally in the Picture Archiving and Communication System (PACS) on standard posterior anterior (PA), lateral carporadial and lateral X-rays of the wrist. Radiographs will be obtained according to standardised procedures. PA radiographs with the shoulder in 90 degrees abduction, elbow in 90 degrees flexion and the wrist in neutral position; lateral X-rays with the shoulder in neutral position and elbow in 90 degrees flexion; and the lateral carporadial radiographs will be obtained by positioning the lower arm on a 20-25 degrees angled wedge.

• Rate of cross-overs

• Complications such as: loss of reduction, fracture malunion or non-union, wound and/or plate infection, tendon irritation and/or rupture, neuropathy and the occurrence of complex regional pain syndrome according to the criteria by Veldman et al. [24].

